Borneol	antibacterial; anti-inflammatory; pain relief; local anesthesia; promote blood–brain barrier permeability; promote drug absorption
Menthol	cooling; pain relief; itch relief; promotes local blood circulation

Patients in the control group will also receive twice daily treatment sessions of urea vitamin E cream and placebo Fuzhiqing ointment for 2 weeks. The placebo Fuzhiqing ointment is made using guar gum as a thickening agent, caramel color as a coloring agent, and purified water as a filler. Therefore, it has the consistency of a traditional Chinese medicinal ointment but does not contain any active ingredients, and as such, does not have therapeutic effects. The placebo Fuzhiqing ointment is produced and provided by the same company, which maintains complete consistency with the Fuzhiqing ointment in terms of appearance, weight, color, odor, and package. The medication guidance and application of placebo Fuzhiqing ointment and urea vitamin E cream in the control group are completely consistent with that in the treatment group. In this study, no additional treatment is permitted during the study. Emergency interventions require documentation in detail and will result in the withdrawal of participation.

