### Outcomes

#### Primary outcome

The primary outcome indicator in this study is the EASI50 achievement rate at week 2. The EASI50 achievement rate is defined as the proportion of patients with mild-to-moderate AD who achieved ≥50% improvement in EASI score from baseline to week 2.

The EASI score includes the affected body surface area score (A) and clinical features score (B) of the head and neck, trunk, upper limbs, and lower limbs (19). (A) involves evaluating the percentage of affected body surface area (BSA) for each part. The percentage of affected BSA for each region is scored on a scale of 0–6: 0 (0%), 1 (<10%), 2 (10–19%), 3 (20–49%), 4 (50–69%), 5 (70–89%), and 6 (90–100%). (B) assesses four key clinical features, including erythema (E), edema/papules/infiltration (I), excoriation (Ex), and lichenification (L). Each feature is scored based on severity, ranging from 0 to 3 points (0 = none, 1 = mild, 2 = moderate, 3 = severe). The EASI score is calculated by multiplying the product of (A) and (B) with regional weighted coefficient (0.1–0.4) and then summing across all regions. The total score of EASI ranges from 0 to 72 points, with higher scores indicating greater severity. According to the EASI score, the skin lesion condition of AD patient is considered as mild (0–7 points), moderate (7–21 points), or severe (>21 points). In this study, the EASI score will be estimated at baseline (week 0), week 1, week 2, and week 6.

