### Statistical analysis

In this study, analysis will be performed by applying SAS 9.4 statistical package. Normally distributed quantitative variables will be summarized as mean and standard deviation (SD), while those with skewed distributions will be presented as median and interquartile range (IQR). The Student *t*-test will be used for inter-group comparison of quantitative variables with normal distribution, while the Wilcoxon rank-sum test will be employed for quantitative data with skewed distribution. The repeated measurement data will be analyzed by repeated measure analysis of variance. Categorical variables will be reported as frequencies and proportions (%), with group differences assessed using chi-square tests or Fisher’s exact tests. In this study, data analysis will adhere to the intention-to-treat (ITT) principle, including all randomized patients regardless of protocol adherence or study completion (25). Missing data will be handled under the missing-at-random assumption using sequential regression multiple imputation, which imputes missing values through regression models for each variable conditional on the other variables (26). Additionally, data analysis will be conducted on both the full analysis set (FAS) and the per-protocol set (PPS), and a *p*-value less than 0.05 (two tailed) is considered as statistically significant.

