Previous studies indicate that Fuzhiqing ointment effectively alleviate neurodermatitis symptoms, improves quality of life, and exhibits a favorable safety profile (32). In addition, clinical study also indicates that the combination of Fuzhiqing ointment and Heparin sodium ointment can improve eczema symptoms by mitigating the release of inflammatory factors and protecting nerve endings, with fewer adverse reactions (33). Furthermore, urea vitamin E cream has been shown to enhance skin hydration, elasticity, and barrier function, with the synergistic effects of urea’s moisture retention and Vitamin E’s antioxidant properties make it widely applicable and well-tolerated across diverse patient populations (37, 38). Therefore, this study design incorporates foundational therapy (urea-vitamin E cream) with rescue medication (cetirizine hydrochloride tablets for refractory pruritus), ensuring all AD participants receive standardized background care throughout the trial. This clinical trial aims to systematically evaluate the therapeutic efficacy of Fuzhiqing ointment in mild-to-moderate AD through multidimensional assessment of core domains: skin lesion severity, pruritus intensity, and quality of life. Study findings will facilitate the adoption of Fuzhiqing ointment in clinical practice as an evidence based therapeutic option for mild-to-moderate AD, offering patients with effective symptom mitigation, reduced disease management expenditure, and optimized sustained disease control.

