This study is subject to several limitations. First, participant recruitment is restricted to individuals with mild-to-moderate AD, enhancing internal validity while potentially limiting the generalizability of findings to broader populations. Second, the protocol mandates a 2-week active treatment phase followed by a 4-week observational follow-up period, which limits the observation of long-term effects of Fuzhiqing ointment, as well as its efficacy of diseases recurrence prevention in patients with AD. Third, differences of climate (temperature, humidity, ultraviolet radiation, seasonal changes), lifestyle habits (high-fatty food consumption, high-calorie diets, tobacco smoking, alcohol drinking) and other extrinsic factors (cultural difference, occupational exposure, etc.) in the 10 selected hospitals may cause information bias. Fourth, patients in this study will be instructed not to use any additional treatment for AD which might induce a relatively high rate of withdrawal.

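### Patients withdrawn after an emergency intervention are imputed under missing-at-random without exception, so a treatment failure before week 2 can count as an EASI50 responder

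*Protocol article*

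**What the plan says.** All statements are in the protocol article.

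- **Primary outcome:** "The primary outcome indicator in this study is the EASI50 achievement rate at week 2". Response means at least 50% improvement in EASI from baseline.
- **Interventions:** "no additional treatment is permitted during the study", and "Emergency interventions require documentation in detail and will result in the withdrawal of participation".
- **Statistical analysis:** the analysis follows intention-to-treat, "including all randomized patients regardless of protocol adherence or study completion". On missing values: "Missing data will be handled under the missing-at-random assumption using sequential regression multiple imputation". Each variable is imputed from a regression on the other variables. No class of withdrawal is exempted.
- **Discussion, limitations paragraph:** patients are told not to use other AD treatment, "which might induce a relatively high rate of withdrawal".
- **Discussion, on the design:** background care is combined with "rescue medication (cetirizine hydrochloride tablets for refractory pruritus").
- **Withdraw and dropout:** the reason for each withdrawal goes into the case report form.
- **Sample size:** assumed response 60% versus 30%, 10% dropout, targets of 140 and 70 patients.

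**The concern.** Three stated rules combine badly. Needing an emergency intervention ends participation. If that happens before week 2, the primary outcome is missing. Every missing outcome is then filled in under MAR. Where the intervention was needed because the skin disease was not controlled, the patient is a treatment failure, yet some imputations will return a response.

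MAR requires that, given the data already recorded, withdrawal says nothing more about the unseen week-2 result. A flare between the week-1 and week-2 visits that leads to emergency treatment and withdrawal breaks that condition. The article itself names the ban on other treatment as a possible cause of much withdrawal.

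At stake is the primary treatment difference. The active arm's imputation draws on a higher response rate, so each withdrawn active patient tends to be credited with more of a response than each withdrawn control patient. Equal withdrawal then widens the absolute difference; unequal withdrawal can move it either way.

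**Working it through.** The plan gives no figure of its own for this effect, so there is none to reproduce.

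**Inputs from the article:** response 60% and 30%; 140 and 70 patients; 10% dropout. **Assumed:** withdrawal by arm, its cause, and how well week 1 predicts week 2. All withdrawals below are taken to be failure-related.

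**Identity.** Let w be the fraction withdrawn in an arm and s the share of those imputed as responders. The difference under MAR imputation exceeds the difference under non-responder counting by

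w(active) × s(active) − w(control) × s(control).

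**Step 1: by hand, no useful week-1 data.** Take s as 0.60 and 0.30.

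- 10% per arm is 14 and 7 patients. Imputation credits 14 × 0.60 = 8.4 and 7 × 0.30 = 2.1 responders. Gap: 0.10 × 0.60 − 0.10 × 0.30 = 3.0 points. Non-responder counting gives 54% versus 27%, a difference of 27 points instead of 30.
- 15% versus 5%: 0.15 × 0.60 − 0.05 × 0.30 = 7.5 points.
- 10% versus 25%: 0.10 × 0.60 − 0.25 × 0.30 = −1.5 points.

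**Step 2: with week-1 data in the imputation model.** Simulation of 1 million patients per arm. Week-1 and week-2 improvement are standard normal with correlation r. Response cut-points give 60% and 30%. The lowest scorers on the driving variable plus noise (SD 0.5) withdraw. Week 2 is imputed by regression on week 1 within arm.

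| Withdrawal follows | r | s active, 10% | s control, 10% | Gap 10%/10% | Gap 15%/5% | Gap 10%/25% |
|---|---|---|---|---|---|---|
| unseen week-2 status | 0.5 | 53% | 21% | +3.2 | +8.0 | −2.2 |
| unseen week-2 status | 0.7 | 35% | 9% | +2.6 | +6.0 | −0.9 |
| observed week-1 status | 0.5 | 28% | 7% | +2.1 | +4.4 | −0.1 |
| observed week-1 status | 0.7 | 15% | 2% | +1.3 | +2.8 | +0.1 |

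Gaps are in percentage points. Check of the first row: 0.10 × 0.532 − 0.10 × 0.208 = 0.032. With noise SD 1 and withdrawal on week-2 status, the active share reaches 54% at r = 0.5.

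The two mechanisms mean different things. In the upper rows almost none of the withdrawn active patients would have responded (0.6%). Non-responder counting stays at about 30 points while imputation gives 32.6 to 33.2, so the gap is bias. In the lower rows imputation correctly returns 30 points for the outcome had nobody left. Non-responder counting gives 27.9 to 28.6, so the gap is a difference of estimand.

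**Step 3: no true difference, 15% versus 5%.** If withdrawal follows week-2 status, imputation shows +1.6 to +2.8 points at a common rate of 30%, and +4.7 to +6.3 at 60%. If it follows week-1 status, imputation shows about zero.

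**The case against.** **Intention-to-treat.** A reader might infer that imputing these patients breaks the intention-to-treat principle. It does not. The article defines that principle as including all randomized patients, and multiple imputation keeps every one of them in. Counting rescue as non-response is a choice of estimand that intention-to-treat does not dictate.

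**Failures filled in from patients who did well.** This overstates it. Imputation is conditional on the other variables, and Table 2 schedules EASI, NRS, IGA, DLQI and ADCT at week 1. A patient doing badly at week 1 is imputed from patients with similar week-1 values. With four week-1 predictors, each correlated 0.7 with week 2 and otherwise independent (favourable to MAR), and withdrawal still following week-2 status, the active share falls to about 11%. The gaps become +1.0 (10%/10%), +2.5 (15%/5%) and +0.1 (10%/25%). This protection is lost when week 1 is also missing.

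**High withdrawal as a forecast.** The limitations paragraph says only that withdrawal might be relatively high. Emergency intervention is not defined and need not mean AD failure, and patients may leave for any reason. So not every withdrawal is a failure, and the documents give no withdrawal rate by arm.

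**The analysis plan may settle it.** Estimand wording and imputation details can properly sit there. The protocol, however, already fixes MAR for all missing data; a non-responder rule elsewhere would change that statement.

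**Small effect.** At 10% per arm, with the Step 1 rates, power at 140 and 70 patients is 98.9% for 60% versus 30% and 97.0% for 54% versus 27%. The conclusion would rarely turn on this at equal withdrawal. That stands, and it limits the severity.

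**Conclusion.** The point holds as a should-fix. Followed as written, the protocol can credit a patient withdrawn for lack of effect before week 2 with an EASI50 response in the primary analysis. Its own remark on withdrawal makes unqualified MAR doubtful.

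The ranges are about 1 to 3 points at 10% withdrawal per arm, about 3 to 8 at 15% active versus 5% control, and zero to about −2 at 10% versus 25%. They rest on assumed correlations of 0.5 to 0.7, one week-1 predictor, and all withdrawals being failure-related. A richer imputation model gives smaller values.

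A reader might infer that the plan inflates the effect or manufactures one. The documents do not support that as a general claim. The direction depends on which arm loses more patients. A spurious difference, about +1 to +6 points at 15% versus 5%, needs both higher withdrawal on active and withdrawal that follows unseen week-2 status. Nothing in the article shows either.

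**What to change.** Before unblinding, amend the Statistical analysis section as follows.

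1. In the primary analysis, a patient withdrawn before week 2 after emergency or rescue treatment for AD, for lack of efficacy, or for a treatment-related adverse event counts as an EASI50 non-responder. The recorded withdrawal reasons identify these patients.
2. MAR multiple imputation applies only to week-2 values missing for other reasons.
3. All-MAR imputation is kept as a sensitivity analysis.
4. Where the patient agrees, week-2 EASI is still recorded after study treatment stops.

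Separately, reconcile the Interventions section, which permits no additional treatment, with the Discussion, which makes a rescue medication part of the design. Together they decide who is withdrawn and imputed. Which rule applies is for the investigators to settle.

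The cost is a few sentences and a note to sites. Both response rates become slightly lower. The composite rule is also not neutral. In Step 3 with withdrawal following week-1 status, it shows 0.4 to 3.6 points against the arm that loses more patients. The all-MAR sensitivity analysis should therefore be reported beside it.

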## Results

In this study, ethics approval was obtained in December 2024 and registered in Chinese Clinical Trial Registry in January 2025. Participant recruitment was commenced in February 2025 and is expected to be completed by February 2026. Data analysis will initiate in May 2026, and the preliminary trial results are expected to be submitted for peer-reviewed publication in December 2026.

## Discussion

This multicenter, randomized, double-blind, placebo-controlled clinical trial represents the first investigation evaluating the efficacy of Fuzhiqing ointment in Chinese patients with mild-to-moderate AD. In this study, the urea-vitamin E cream and Fuzhiqing ointment combination is anticipated to effectively alleviate AD symptoms in mild-to-moderate cases, potentially offering a novel therapeutic approach for AD management. AD profoundly impacts the physical and mental health of patients, suffering from itching, impaired self-image, social disturbance and somnipathy for a long time. Moreover, AD imposes substantial burdens on daily academic, occupational, and personal functions, contributing to significantly elevated risks of anxiety and depression among those affected individuals (27, 28). Meanwhile, AD imposes a substantial additional physical and mental burden on adolescents, adversely affecting their learning, social development, and self-esteem formation (29, 30). For AD treatment, the anti-inflammatory agents, wet wrap therapy, systemic immunology-suppressants and short-term steroid treatment are used to manage persistent or severe AD cases. Although glucocorticoids exhibit therapeutic efficacy for patients with mild-to-moderate AD, long-term application can induce adverse cutaneous effects, including skin dryness, atrophy, stratum corneum weakening, pigmentation, and superficial capillary dilation. Furthermore, the long-term application of glucocorticoids may impair skin barrier, disrupt surface microbial communities, and exacerbate inflammatory reactions within skin tissue (31). These limitations underscore the persistent clinical need for novel topical therapies with improved safety, efficacy, and manageability.

Fuzhiqing ointment replenishes moisture and lipids, restoring the skin’s natural barrier, reducing transepidermal water loss, and maintaining its physiological acid–base balance (32). Besides, the ointment might modulate the skin microbiome by inhibiting harmful bacteria like *Staphylococcus aureus* and supporting beneficial microbes, potentially reducing inflammation. Meanwhile, its immune-modulatory effects might restore immune homeostasis by downregulating Th2-driven inflammation and promoting regulatory T cell activity (33). These mechanisms suggest that Fuzhiqing ointment could provide a multifaceted approach to AD management, but further clinical studies are needed to confirm its efficacy and underlying mechanisms. In the treatment of skin disease, herbal topical treatments and emerging biologics, such as dupilumab, exhibit distinct efficacy profiles. Herbal remedies are effective for mild to moderate cases, offering gentle symptom relief and improving skin barrier function, though their effects are often slower and less potent. In contrast, biologics target immune pathways, providing rapid and robust improvement in severe cases, but with higher costs and potential side effects (34–36). Therefore, herbal topical treatments, with their effectiveness, high safety profile, and lower cost, still offer significant advantages in the treatment of mild to moderate skin conditions.

Previous studies indicate that Fuzhiqing ointment effectively alleviate neurodermatitis symptoms, improves quality of life, and exhibits a favorable safety profile (32). In addition, clinical study also indicates that the combination of Fuzhiqing ointment and Heparin sodium ointment can improve eczema symptoms by mitigating the release of inflammatory factors and protecting nerve endings, with fewer adverse reactions (33). Furthermore, urea vitamin E cream has been shown to enhance skin hydration, elasticity, and barrier function, with the synergistic effects of urea’s moisture retention and Vitamin E’s antioxidant properties make it widely applicable and well-tolerated across diverse patient populations (37, 38). Therefore, this study design incorporates foundational therapy (urea-vitamin E cream) with rescue medication (cetirizine hydrochloride tablets for refractory pruritus), ensuring all AD participants receive standardized background care throughout the trial. This clinical trial aims to systematically evaluate the therapeutic efficacy of Fuzhiqing ointment in mild-to-moderate AD through multidimensional assessment of core domains: skin lesion severity, pruritus intensity, and quality of life. Study findings will facilitate the adoption of Fuzhiqing ointment in clinical practice as an evidence based therapeutic option for mild-to-moderate AD, offering patients with effective symptom mitigation, reduced disease management expenditure, and optimized sustained disease control.

This study is subject to several limitations. First, participant recruitment is restricted to individuals with mild-to-moderate AD, enhancing internal validity while potentially limiting the generalizability of findings to broader populations. Second, the protocol mandates a 2-week active treatment phase followed by a 4-week observational follow-up period, which limits the observation of long-term effects of Fuzhiqing ointment, as well as its efficacy of diseases recurrence prevention in patients with AD. Third, differences of climate (temperature, humidity, ultraviolet radiation, seasonal changes), lifestyle habits (high-fatty food consumption, high-calorie diets, tobacco smoking, alcohol drinking) and other extrinsic factors (cultural difference, occupational exposure, etc.) in the 10 selected hospitals may cause information bias. Fourth, patients in this study will be instructed not to use any additional treatment for AD which might induce a relatively high rate of withdrawal.

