### Sample size

The sample size was calculated based on the EASI50 achievement rate at week 2, which was defined as the proportion of patients who achieved ≥50% improvement in Eczema Area and Severity Index (EASI) score from baseline to week 2. According to previous evidence, we assume that the EASI50 achievement rate at week 2 was 60% in the treatment group and 30% in the control group (18). The sample size calculation for a 2:1 randomization design performed in PASS 15.0 (NCSS Statistical Software) indicates that 116 patients in the treatment group and 58 patients in the control group need to recruit with a 2-tailed *α* level of 0.05 and a statistical power of 80%. Considering a dropout rate of 10 and 10% multicenter effect, the final enrollment targets are 140 patients in the treatment group and 70 patients in the control group.

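### The Discussion makes cetirizine a rescue medication of the trial, while Interventions bans additional treatment without exception, so the article supports two handlings of a cetirizine user

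*Protocol article*

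**What the plan says.** Three places in the protocol article bear on what happens to a patient given cetirizine.

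- **Discussion, paragraph on previous studies:** "this study design incorporates foundational therapy (urea-vitamin E cream) with rescue medication (cetirizine hydrochloride tablets for refractory pruritus"). The same sentence adds that this gives every participant uniform baseline care for the whole trial.
- **Interventions:** "no additional treatment is permitted during the study. Emergency interventions require documentation in detail and will result in the withdrawal of participation". No drug is exempted, and cetirizine is not mentioned in the description of either arm's regimen.
- **Discussion, limitations:** "patients in this study will be instructed not to use any additional treatment for AD which might induce a relatively high rate of withdrawal".

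Cetirizine appears nowhere else. The study schedule (Table 2) and the case report form record concomitant medication but do not say which drugs are allowed.

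On the analysis, the Statistical analysis section follows the intention-to-treat principle, "including all randomized patients regardless of protocol adherence or study completion", and says: "Missing data will be handled under the missing-at-random assumption using sequential regression multiple imputation". The sample size allows for losses in these words: "Considering a dropout rate of 10 and 10% multicenter effect".

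**The concern.** Read literally, Interventions forbids the drug that the Discussion builds into the design. A patient with refractory itch who is given cetirizine could be seen as using planned rescue and continuing, as breaking the ban, or as having had an emergency intervention and therefore being withdrawn.

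The choice matters because refractory itch is a sign of poor response. Withdrawal triggered by it is linked to the outcome, and its frequency may differ between arms. A withdrawn patient stays in the intention-to-treat set. If no week 2 assessment is made, though, the primary outcome is filled in by a model that assumes missingness is explained by the observed data. Week 1 scores would carry part of that link, not all of it.

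If users continue instead, the outcomes most directly exposed are the itch-related ones. The pruritus NRS asks for peak itch over the preceding 24 hours, ADCT counts severe itching episodes, and DLQI is likely to follow itch. An antihistamine can lower these scores in whichever arm uses it more. Membership of the per-protocol set depends on the same rule.

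**Working it through.** **1. The texts side by side**

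| Question | Interventions | Discussion (design) | Discussion (limitations) |
|---|---|---|---|
| Is cetirizine allowed? | No additional treatment; no exemption | Yes, as rescue for refractory itch | No additional treatment for AD |
| Is a user withdrawn? | Yes, if its use counts as an emergency intervention; otherwise not stated | Not stated; baseline care for the whole trial suggests no | Ban expected to raise withdrawals |

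The texts agree only if additional treatment means treatment beyond what the design supplies. Interventions does not say so. The Introduction lists antihistamines among treatments for AD, so cetirizine falls within the ordinary meaning of the ban.

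**2. How much the primary estimate could move (illustration)**

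From the Sample size section: week 2 EASI50 of 60% against 30%, 140 and 70 patients, 10% dropout.

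Assumed, because the document gives no figures: cetirizine users respond at q = 10% in both arms; all 21 planned dropouts (10% of 210) are cetirizine users withdrawn before week 2; withdrawal means no week 2 EASI.

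Let P be the true arm rate and r the share of the arm using cetirizine. If users are withdrawn and imputed at the non-users' rate, the arm estimate is (P − r·q)/(1 − r).

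- *Users observed:* 60 − 30 = 30.0 points.
- *Case A, 7/140 and 14/70 (5% and 20%):* (0.60 − 0.005)/0.95 = 0.626; (0.30 − 0.02)/0.80 = 0.350; difference 27.6 points.
- *Case B, 14/140 and 7/70 (10% each):* (0.60 − 0.01)/0.90 = 0.656; (0.30 − 0.01)/0.90 = 0.322; difference 33.3 points.

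These cases ignore week 1 data. The planned imputation conditions on other variables, so a simulation (2,000,000 patients per arm) used latent normal week 1 and week 2 scores with correlation ρ, made use depend on week 2 response so that users respond at 10%, and imputed users from non-users with the same week 1 score.

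| ρ | Case A | Case B |
|---|---|---|
| 0.5 | 28.0 | 32.8 |
| 0.6 | 28.2 | 32.6 |
| 0.7 | 28.4 | 32.2 |
| 0.8 | 28.7 | 31.9 |

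Against 30.0, the shift is 1.3 to 2.0 points down in case A and 1.9 to 2.8 points up in case B.

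**3. Against sampling error**

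- All 210 observed: SE = √(0.6·0.4/140 + 0.3·0.7/70) = 0.0687, or 6.9 points; power 98.9% (two-sided 0.05).
- Case A, 133 + 56 observed, 62.6% vs 35.0%: SE 7.6 points, power about 94%.
- Case B, 126 + 63 observed, 65.6% vs 32.2%: SE 7.3 points, power about 99.4%.

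Power is taken at the observed numbers because imputed patients add little information. Using 140 + 70 would give 97.1% in case A, which is too favourable.

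**4. Users counted as non-responders (the proposed sensitivity analysis)**

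Each arm rate becomes P − r·q. Case A: 59.5 − 28.0 = 31.5 points. Case B: 59.0 − 29.0 = 30.0 points.

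**The case against.** The strongest reply is that the Discussion largely answers the question. It places cetirizine within the design and within care that all participants receive throughout, which fits badly with withdrawal on use. Additional treatment would then mean anything beyond what the design provides. An oral antihistamine named in advance is not obviously an emergency intervention, and the limitations paragraph bans only further AD treatment. This stands in part: permission is the better-supported reading. It does not remove the conflict, because Interventions describes both regimens down to order, amount and massage and still omits cetirizine.

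A reader might infer that sites do not know what to do with a cetirizine user. The article does not support that. Sites work from the full protocol, which is not shown and may set out rescue rules and permitted medication. What can be said is that the published statements do not agree, which is different from a detail being left out.

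A reader might also infer that the primary result will be biased. That requires sites to withdraw users, use to occur before week 2 although follow-up runs to week 6, withdrawal to mean no week 2 assessment, and users to respond worse than others. None of these is established by the document.

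Finally, EASI scores visible signs and not itch, so the primary outcome is less directly exposed to an antihistamine than the NRS or ADCT. This also stands, and the fix covers those outcomes.

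**Conclusion.** The point holds as an inconsistency in the published article: cetirizine is a rescue medication in the Discussion and falls under an unqualified ban in Interventions, with the balance of wording towards permission. It is worth correcting, with medium confidence, because following Interventions as written could remove poor responders and leave their primary outcome to missing-at-random imputation.

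The likely effect on the primary comparison is small. Under the assumed rates, with week 1 used in the imputation, it is about 1 to 3 points in either direction, less than half of a standard error of about 7 points, and power is about 94% or more. What is exposed is the size of the estimate more than the significance test. These figures rest on assumed rescue rates, a 10% response among users and assumed week 1 to week 2 correlations of 0.5 to 0.8. They are not bounds.

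**What to change.** 1. State in Interventions that cetirizine for refractory pruritus is the one permitted rescue, is recorded with dates and does not cause withdrawal.
2. Let patients who use it, or who need an emergency intervention, stop study treatment if necessary but still attend the week 2 and week 6 assessments.
3. Analyse observed week 2 EASI50 regardless of rescue, in line with the intention-to-treat statement. Add a sensitivity analysis that counts rescue users before week 2 as non-responders.
4. Report cetirizine use by arm and take it into account when reading pruritus NRS, DLQI and ADCT.
5. Align Interventions and both Discussion paragraphs with this rule.

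If the full protocol already says this, the cost is a correction to the article. If not, it is a wording amendment and a memo to the ten sites. The Results section reports that "Participant recruitment was commenced in February 2025 and is expected to be completed by February 2026", so any week 2 assessments already missed through withdrawal cannot be recovered. The number of such patients should be reported by arm.
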